**Inclusion criteria**
• First-ever acute ON
• Onset of visual symptoms within maximum of 30 days
• Age ≥ 18 years
• Ability to give written informed consent
• Presence of written consent
**Exclusion criteria**
• MRI contraindication
• Prior demyelinating diagnosis
• Diagnosis of other forms of optic neuropathy (hereditary, granulomatous, infectious, infiltrative, toxic, incidental signs of prior optic neuropathy, prior events of visual loss, clinical evidence of optic nerve thinning at presentation)
• Pregnancy at inclusion
• Relevant other diseases that conflict with study participation according to protocol
• Inability to cooperate
**Drop-out criteria**
• Withdrawal of consent
• Non-compliance with the protocol (decision by study board)
• Condition hindering study continuation (decision by study board)

MRI, magnet resonance imaging; ON, optic neuritis.

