### Study design

ACON is an international, multicenter non-interventional study network aiming to optimize treatment decisions in subjects with acute ON and to improve understanding of the underlying pathologies. It currently includes 28 teaching hospitals from Africa (Botswana, Zambia), Asia (India, Korea, Thailand, and Vietnam), the Middle East (Israel), North America (USA), South America (Argentina, Brazil, and Colombia), Australia, and Europe (Denmark, France, Germany, Italy, Spain, and United Kingdom) (for details see Supplementary material).

ACON centers will recruit and prospectively collect data from all subjects with inaugural acute ON (see study population).

Local staff will have confirmed up-to-date training in the conduct of studies according to the International Conference on Harmonization of Technical Requirements for Registration of Pharmaceuticals for Human Use (ICH) and good clinical practice (GCP) standards.

All study participants will be evaluated during hospitalization or through outpatient clinics at the time of presenting with inaugural acute ON as well as during follow-ups (at 6- and 12-month after onset). Visits at additional time points are optional, based on patient-tailored needs and the recruiting centers' standard of care. The recruitment period is planned for 36 months. Acute ON treatment is provided as part of routine care according to the clinical best practice at the respective study center. This study will not include the randomization of patients to receive early or late high-dose corticosteroids. Disease diagnosis will be assessed at 6- and 12-month follow-up visits, respecting the diagnostic criteria for MS according to the 2017 revised McDonald criteria (54), diagnosis of AQP4-IgG-positive or seronegative NMOSD according to the 2015 international consensus diagnostic criteria (55), and diagnosis of MOGAD in subjects with clinical characteristics consistent with MOGAD and positive testing of MOG-IgG with respect to the new MOGAD diagnostic criteria (44, 56, 57).

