The exclusion criteria comprise other forms of optic neuropathy (e.g., glaucoma, Leber's hereditary optic neuropathy, other inherited optic neuropathies such as OPA1/OPA3-mutations, granulomatous, infectious, infiltrative, or toxic neuropathies, as well as incidental signs of prior optic neuropathy, prior events of visual loss, and clinical evidence of optic nerve thinning at presentation), other significant comorbidities (i.e., medically uncontrolled severe arterial hypertension, severe diabetes mellitus, chronic infectious diseases, drug abuse, and severe psychiatric or psychological disorders), prior demyelinating diagnosis, pregnancy at inclusion, MRI contraindications, and medical or psychological constraints impacting the ability to give informed consent to study participation and fulfill the study protocol.

The inclusion and exclusion criteria are summarized in Table 2. They are applied at the time of screening by the study physician. Throughout the study duration, we will apply drop-out criteria (see Table 2) as a guideline to evaluate the case for a premature end-of-study.

**Table 2 T2:** Inclusion and exclusion criteria.

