### Medical history and clinical examination

The medical history will be gathered at each visit and consists of demographics (age, sex, race), height and weight, acute attack-related symptoms with a focus on visual symptoms and pain, vaccination history, previous infections, fertility history, comorbidities, and treatment (drugs and supportive therapies).

For acute ON treatment, ACON specifies the following list of treatment options from which each center will select their choice:

(1) IVMP 1 g for 3 days followed by a taper(2) IVMP 1 g for 5 days followed by a taper(3) IVMP 1 g for 3 days without taper(4) IVMP 1 g for 5 days without taper(5) Oral prednisone 1,250 mg every other day (EOD)(6) Others, specified.

In patients with severe visual loss (6/60 or worse) or mean visual field defect of −12 MD and worse at presentation, we recommend rechecking high-contrast best-corrected visual acuity (HC-BCVA) and visual fields on day 5 of IVMP. If vision is not improved by 2 or more lines or more than 4 DB on the visual field, we recommend to consider starting escalation treatment.

For escalation therapy, ACON proved the following treatment suggestions for patients whose vision does not improve with IVMP:

(1) PLEX for 5 days and then reassess vision(2) Immunoadsorption(3) IVIG at the dose of 2 g/kg over 5 days (0.4 per day).

At follow-up, all recurrent ON events as well as all demyelinating events will be captured. We will also capture and describe treatment complications and any other comorbidities occurring during the study period.

The neurological examination includes an Expanded Disability Status Scale (EDSS) according to neurostatus definitions (58, 59). The visual examination measures refraction by an autorefraction device or through direct skiascopy/retinoscopy, 100% high-contrast visual acuity, and 2.5% low-contrast visual acuity measured with Sloan charts, automated visual fields (24-2 or 30-2), and visual evoked potentials (VEP).

HC-BCVA and visual fields are the two visual parameters used globally to define blindness. In addition, HC-BCVA and visual fields are used to determine which patients have a vision that allows driving. Thus, these are two of the most clinically relevant endpoints for the patients themselves (3). Low-contrast best-corrected visual acuity (LC-BCVA) is used as a more sensitive measure of visual dysfunction (60) and will be measured in the acute setting and during follow-up.

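### Table 2 lets the study board end participation for non-compliance or an intercurrent condition in a study that only observes, which can create avoidable and possibly outcome-related attrition

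*Protocol article*

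**What the plan says.** The Drop-out criteria block of Table 2 has three entries. One is withdrawal of consent. The other two are decisions of the study board: "Non-compliance with the protocol (decision by study board" and "Condition hindering study continuation (decision by study board". The Study population section explains their use: over the whole duration of the study, "we will apply drop-out criteria (see Table 2) as a guideline to evaluate the case for a premature end-of-study".

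The Study design section describes the setting: "ACON is an international, multicenter non-interventional study network", and "Acute ON treatment is provided as part of routine care according to the clinical best practice at the respective study center". Follow-up visits are "at 6- and 12-month after onset", and the Data collection section ties data collection to each institution's standard of care.

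The Medical history and clinical examination section commits the study to recording recurrent optic neuritis and other demyelinating events. It adds: "We will also capture and describe treatment complications and any other comorbidities occurring during the study period". The Statistical analysis section groups patients by their diagnosis at the 6-month visit and admits only MS, AQP4-IgG+ NMOSD and MOGAD to the primary analysis.

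**The concern.** In a trial of an assigned treatment, a board may need the power to take a patient off the regimen. ACON has no assigned regimen. A patient who misses a test, departs from the visit schedule or falls ill can still be observed, because acuity and clinical events arise in ordinary care.

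The second board criterion can also overlap with what the study wants to learn. A relapse, a treatment complication or a new illness is something to be recorded, and it could also be the reason a patient is taken out. If removal is related to later vision, the described outcomes are distorted. If it also differs between days-to-treatment strata, so is the early-versus-late comparison. An analysis plan can model missing values, but it cannot recover acuity or events that were never collected.

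**Working it through.** The article states no drop-out rate and no figure for the effect of drop-out, so there is no published number to reproduce. The check has two parts.

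**1. The sections side by side**

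- *Is there a regimen to comply with?* No. Treatment is routine care (Study design). Non-compliance with the protocol can then only mean departures from visits, tests or other study procedures. Table 3 marks many tests as mandatory at 6 and 12 months, so a patient could miss one while acuity is still obtainable.
- *Can a hindering condition be something the study records?* Yes. Relapse history, comorbidities, depression score and pregnancies are all scheduled at both follow-up visits in Table 3.
- *Does an early end reach the primary analysis?* Yes, if it falls before month 6, because grouping uses the 6-month diagnosis (Statistical analysis). A patient ended after month 6 has a diagnosis and a 6-month acuity and could still contribute to the mixed model.
- *Is this loss discussed?* The section on potential bias covers selection at presentation, confounding and information bias. It does not mention loss initiated by the study.

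**2. Size under assumed inputs**

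Let *d* be the share removed from a stratum, and *g* the amount by which removed patients are worse than retained ones, in SD of acuity. Assume removed patients contribute no outcome. The stratum mean then looks better by *d* × *g*, and the contrast between two strata with the same *g* shifts by *g* × (*d*₁ − *d*₀). All values of *d* and *g* are assumptions.

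| *g* (SD) | *d*₁ vs *d*₀ | Shift in contrast (SD) | Shift in mean of the first stratum (SD) |
|---|---|---|---|
| 0 | any | 0 | 0 |
| 0.5 | 10% vs 10% | 0.5 × 0 = 0 | 0.05 |
| 0.5 | 10% vs 5% | 0.5 × 0.05 = 0.025 | 0.05 |
| 0.5 | 20% vs 5% | 0.5 × 0.15 = 0.075 | 0.10 |
| 1.0 | 10% vs 5% | 1.0 × 0.05 = 0.05 | 0.10 |
| 1.0 | 20% vs 5% | 1.0 × 0.15 = 0.15 | 0.20 |

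A count of patients gives the upper end. Sample size considerations plans 50 patients in each antibody group over three strata. If the strata are equal (an assumption), each has 50/3 ≈ 17. Set the stratum mean to 0, with positive values worse:

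- Removing one patient at +2 SD leaves a mean of −2/16 = −0.125 SD.
- Removing two at +2 SD leaves −(2 × 2)/15 = −0.27 SD.
- If acuity were normal, the two worst of 17 would be expected at about 1.79 and 1.32 SD. Removing them leaves −(1.79 + 1.32)/15 = −0.21 SD.
- In MS-ON (100 patients, about 33 per stratum), removing two at +2 SD leaves −4/31 = −0.13 SD.

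For scale, the 95% half-width for a contrast between two strata of 50/3 patients is 1.96 × √(2 × 3/50) = 0.68 SD. The shifts are smaller than this sampling uncertainty, but they are systematic and would not average out with more patients.

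**The case against.** The case against is substantial, and most of it stands against stronger readings of the rule.

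- *A reader might infer that the rule removes the patients with the worst vision or most complications.* No section links either criterion to vision, relapse or complications. Non-compliant patients could equally be those who recovered well and stopped attending. Table 3 schedules relapses, depression and pregnancies as follow-up data, and pregnancy is an exclusion only at entry. The documents support only that such patients may be among those removed.
- *A reader might infer automatic removal.* The criteria serve "as a guideline to evaluate the case for a premature end-of-study", so the board retains judgement.
- *A reader might infer that data are discarded, or that the board sees exposure and outcome when it decides.* The article says neither. Retention rules, board procedures and missing-data handling may sit in the full protocol, a charter or the analysis plan, so silence on them is not counted here.
- *A reader might say nothing could ever justify ending participation.* The study includes venous sampling and contrast MRI, and patients must be able to consent and cooperate. A patient who loses capacity may have to stop. That is a reason to stop procedures or to respect the limits of consent, and it does not require acuity recorded in ordinary care to be lost in every other case.
- *A reader might say any bias could never be examined.* Baseline acuity and treatment history are mandatory, so removed and retained patients can be compared on both. The comparison cannot supply the missing outcomes.
- *A reader might take 0.27 SD as an estimate.* It is close to a worst case: the smaller disease groups, equal strata, both removals in one stratum, and both patients 2 SD from the mean.

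What survives is the stated rule itself. It gives the study a way to end observation that its design does not need.

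**Conclusion.** The point holds as a risk created by a written rule. The board may end participation for protocol non-compliance or a hindering condition in a study that assigns nothing and observes routine care. This can produce avoidable, possibly outcome-related attrition, and a removal before month 6 leaves the patient without the diagnosis needed for the primary analysis.

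The document does not allow direction or size to be derived. Under the assumptions shown, the shift in a stratum mean or contrast runs from about 0.03 to 0.27 SD. It is zero when removed and retained patients have the same outcomes. Equal removal with an equal gap leaves the contrast unbiased and shifts only the described level. The range also assumes that removed patients contribute no outcome, which need not be true after month 6.

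The plan should be changed here. Nothing in the article shows that the rule has biased, or will bias, the result.

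**What to change.** Replace the two board criteria in Table 2, and align the sentence in Study population, along these lines:

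> Participation ends early only on withdrawal of consent, death, or true inability to obtain any further data. Missed visits or tests, protocol deviations and intercurrent conditions do not end participation; assessments that cannot be done are left out. Within the scope of consent, all data already collected are kept, and visual acuity, diagnosis, relapses and complications continue to be recorded from routine care to 12 months. The reason for every early end is logged and reported by diagnosis and days-to-treatment stratum.

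The study should also add attrition to the section on potential bias.

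Cost: a wording change, and some retained patients with incomplete secondary data. Because ethics approvals are obtained separately by each of the 28 centres, centres may also need to confirm that consent covers continued collection from routine care.

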### Data collection

Screening for study eligibility occurs at the time of presentation at the respective study center. Data collection according to the standard of care at the respective institution is performed in the acute phase of an inaugural acute ON (baseline visit) and at 6- and 12-month follow-up visits.

### Medical history and clinical examination

The medical history will be gathered at each visit and consists of demographics (age, sex, race), height and weight, acute attack-related symptoms with a focus on visual symptoms and pain, vaccination history, previous infections, fertility history, comorbidities, and treatment (drugs and supportive therapies).

For acute ON treatment, ACON specifies the following list of treatment options from which each center will select their choice:

(1) IVMP 1 g for 3 days followed by a taper(2) IVMP 1 g for 5 days followed by a taper(3) IVMP 1 g for 3 days without taper(4) IVMP 1 g for 5 days without taper(5) Oral prednisone 1,250 mg every other day (EOD)(6) Others, specified.

In patients with severe visual loss (6/60 or worse) or mean visual field defect of −12 MD and worse at presentation, we recommend rechecking high-contrast best-corrected visual acuity (HC-BCVA) and visual fields on day 5 of IVMP. If vision is not improved by 2 or more lines or more than 4 DB on the visual field, we recommend to consider starting escalation treatment.

For escalation therapy, ACON proved the following treatment suggestions for patients whose vision does not improve with IVMP:

(1) PLEX for 5 days and then reassess vision(2) Immunoadsorption(3) IVIG at the dose of 2 g/kg over 5 days (0.4 per day).

At follow-up, all recurrent ON events as well as all demyelinating events will be captured. We will also capture and describe treatment complications and any other comorbidities occurring during the study period.

The neurological examination includes an Expanded Disability Status Scale (EDSS) according to neurostatus definitions (58, 59). The visual examination measures refraction by an autorefraction device or through direct skiascopy/retinoscopy, 100% high-contrast visual acuity, and 2.5% low-contrast visual acuity measured with Sloan charts, automated visual fields (24-2 or 30-2), and visual evoked potentials (VEP).

HC-BCVA and visual fields are the two visual parameters used globally to define blindness. In addition, HC-BCVA and visual fields are used to determine which patients have a vision that allows driving. Thus, these are two of the most clinically relevant endpoints for the patients themselves (3). Low-contrast best-corrected visual acuity (LC-BCVA) is used as a more sensitive measure of visual dysfunction (60) and will be measured in the acute setting and during follow-up.

### Pain, depression, visual function in daily routine, and QoL assessment

We will assess pain patterns using a semi-standardized interview. Questions focus on ON-related headache characteristics including the onset of pain, pain intensity, pain quality, location, duration, additional symptoms, response to pain treatment, and pain response to steroid treatment. Second, the Brief Pain Inventory (BPI) will be performed to assess (1) pain severity within the previous 24 h and (2) seven domains of pain-related interference with daily life including general activity, mood, walking ability, working ability, relations with other people, sleep, and enjoyment of life (61). The Beck's Depression Inventory version II (BDI-II) will be used to capture signs of depression both in the acute phase and during follow-ups (62). Visual quality function in daily routine is measured with the National Eye Institute Visual Function Questionnaire (NEI-VFQ-25), with its neuro-ophthalmological supplement (63). QoL is measured with the EuroQol 5-dimension (EQ-5D) index in five dimensions: mobility, self-care, usual activities, pain/discomfort, and anxiety/depression (64).

### Biosampling

Blood and CSF will be collected within one week from the presentation. Venous blood samples will be collected, comprising of serum, plasma, as well as optional PAXGen and peripheral blood mononuclear cell (PBMC) vials. Biosample analysis includes a clinical standard laboratory diagnostic panel as well as testing for AQP4- and MOG-antibodies, GFAP, and NfL. Systematic serum antibody measurements including AQP4-IgG and MOG-IgG will be performed with fixed or live cell-based assays (CBA) (65–67). MOG-IgG samples will be tested and reconfirmed employing both the commercially available assay and the human cell-based assay. Cell-based assays for MOG-IgG will either be performed at centers at which this assay is available (Mayo clinic, Barcelona, etc.) or shipped to a participating ACON center to reconfirm fixed cell-based assays.

CSF will be obtained from clinical routine diagnostics (only in the acute phase) and collected for further analysis at the respective center. Routine diagnostics include oligoclonal band detection and cell count. In addition to a clinical standard CSF analysis, MOG-IgG in CSF will be assessed. Preserves of biospecimens will be stored at −80°C for future scientific analyses.

### Magnetic resonance imaging

Cerebral MRI with dedicated orbital cuts at the baseline will be performed as part of the clinical routine diagnostic tests. Patients will receive 1.5 or 3-Tesla imaging, including a cerebral 3D T2-weighted and/or Fluid Attenuated Inversion Recovery (FLAIR) sequence, and, if available, a 3D T1-weighted Magnetization Prepared Rapid Gradient Echo (MPRAGE) sequence. In the acute setting and at 6-month follow-up, 3D T1-weighted, fat suppression (FS) sequences and/or MPRAGE will be performed following gadolinium administration. Radiological analysis parameters include brain lesion number and volume, location, and extension (for details see Supplementary material Questionnaires and Data Collection CRFs). The MRI characterization score of the optic nerve developed by Ramanathan et al. (28) takes into account optic nerve lesion extent and character, as well as the presence or absence of abnormalities in other parts of the brain.

### Optical coherence tomography

Participants will undergo OCT of the retina and the optic nerve head within 10 days from the presentation. The following Spectral Domain OCT devices will be included: Cirrus HD-OCT, Carl Zeiss Meditec, Jena, Germany; Topcon, Optovue, Canon or Spectralis, Heidelberg Engineering, Heidelberg, Germany.

Scans will be obtained in adherence to the Advised Protocol for OCT Study Terminology and Elements (APOSTEL) 2.0 nine-point recommendations and the OSCAR-IB quality criteria (68, 69). Documented OCT measurements include the average pRNFL thickness, GCL or GCC as collected by the different platforms (e.g., Spectralis measuring GCL, Zeiss measuring GCC). The OCT images will subsequently be analyzed using *post-hoc* analysis with semi-automatic, device-independent algorithms (70).

We will exclude patients with insufficient documentation or those who have their OCT imaging on time-domain devices. Low-quality spectral-domain OCT data will be excluded from the OCT analysis. We plan to qualitatively explore concomitant OCT findings, including microcystic macular oedema (MMO) or peripapillary hyperreflective ovoid mass-like structures (PHOMS) (71, 72).

Table 3 summarizes the data collection.

**Table 3 T3:** Data collection overview.

**Collected data type**	**Study Enrollment (Screening)**	**Baseline**	**6 months follow-up**	**12 months follow-up**	**Additional study visits (optional)**
Patient demographics	X				
Informed consent	X				
Inclusion/exclusion criteria	X				
Race		X			
Semi-structured assessment of patient reported visual symptoms		X	X	X	(X)
Semi-structured pain assessment		X	X	X	(X)
Treatment history		X	X	X	(X)
Medical history and comorbidities		X	X	X	(X)
Pregnancies		X	X	X	(X)
Vaccination history		X	X	X	(X)
Relapse history		X	X	X	(X)
BPI		X	X	X	(X)
BDI-II		X	X	X	(X)
EQ-5D		(X)	(X)	(X)	(X)
Visual function in daily routine (NEI-VFQ-25 + neuro-ophthalmological supplement)		(X)	(X)	(X)	(X)
Vital signs and measurements		X	X	X	(X)
Clinical routine laboratory tests from serum and CSF, including OCB, AQP4-IgG, MOG-IgG		X	X	X	(X)
Biomarker analysis (GFAP, NfL)		X	X	X	(X)
EDSS		X	X	X	(X)
High-contrast visual acuity		X	X	X	(X)
Low-contrast visual acuity		X	X	X	(X)
Automated visual fields (24-2 or 30-2)		(X)	(X)	(X)	(X)
VEP		(X)	(X)	(X)	(X)
Cerebral MRI, including orbital cuts (lesion number, lesion volume, lesion location, number of involved segements by the ON)		X	(X)	(X)	(X)
OCT (pRNFL, macular ganglion cell analysis, morphometric markers)		X	X	X	(X)

X without brackets indicates mandatory tests, (X) indicates optional tests. AQP4, aquaporin-4; BPI, Brief Pain Inventory; CSF, cerebrospinal fluid; EDSS, Expanded Disability Status Scale; EQ-5D, EuroQol 5-Dimension EQ-5D-index; GFAP, glial fibrillary acidic protein; MRI, magnet resonance imaging; MOG, myelin-oligodendrocyte glycoprotein; NEI-VFQ-25, National Eye Institute Visual Function Questionnaire; NfL, neurofilament light chain; OCB, oligoclonal bands; OCT, optical coherence tomography; ON, optic neuritis; pRNFL, peripapillary retinal nerve fiber layer; VEP, visual evoked potentials.

